#### Project B: cortical reorganisation and compensation strategies

30 patients each from the A1 and A2 projects will be asked to participate in project B. They will undergo haptic robot measurements and TMS at set times, while only patients that can extend their wrist beyond 10 degrees and fingers beyond 20 degrees will be asked to participate in the fMRI measurements.

#### Project C: longitudinal relations

There will be no extra measurements for project C. All necessary data are derived from project A and B.

*4.6 Time schedule*

###### Therapy

- CIMT *or* EMG-NMS *or* conventional therapy: week 1 t/m 4

Clinical assessment in Project A:

- ARAT week 1,2,3,4,5,8,12,26
- AS
- MI-arm
- MI-leg
- FM-arm
- LCT
- 9-NHP
- EmNSA
- FAT
- NIHSS
- WMF test week 1,12,26

###### Questionnaires in Project A

- NEADL week 1,2,3,4,5,8,12,26
- MAL
- SIS-3.0 week 1,12 en 26

###### Assessments not requiring direct patient contact

- BI week 1,2,3,4,5,8,12,26

Total time of measurements is approximately 1 hour. When WMF test and SIS are included (at 12 and 26 weeks) total assessment time is approximately 2 hours

###### Additional clinical assessment in Project B

- fMRI week 2, 5 en 26
- TMS week 2, 5 en 26 ( MEP in week 1)
- Haptic robot week 1,2,3,4,5,8,12,26
- Kinematics week 2,3,4,8,26

See also appendix 2

*4.7 Burden and risks*

We are aware of the burden on patients of early intervention and clinical measurements in their early stage of recovery. However, evidence is compelling that in the first weeks after stroke functional outcome is determined. If the treatment has to have any effect on primary outcome it should be applied in the early phase after stroke. Next to the opportunity to evaluate early applied intensive therapy we expect to find answers to fundamental research questions that are vital to our understanding of functional recovery after paresis of the upper limb, which is a prerequisite for future optimal treatment planning.

###### Clinical assessment

Assessment of the patients is performed by a combination of questionnaires and (functional) tasks. There are no invasive measurements. Care is taken that the total time to perform all the required assessments is no more than 1 hour

###### Project A1

The treatment group will receive Constraint Induced Movement Therapy (CIMT) for 5 days a week for three weeks. CIMT consist of immobilizing the unaffected hand with a padded safety mitt (appendix 3) in combination with functional therapy (task oriented exercises, “shaping”) by a Physical Therapist (PT). The exercises last 30 minutes, after which the unaffected arm is immobilized for 3 hours. The risks of the treatment are minimal. The method is not invasive

###### Project A2

EMG-NMS allows for electrostimulation of the affected hand without continuous support of a therapist. Once the patient or his/her spouse has learned to use the apparatus, the therapy can be applied without the need of continuous focusing of the patient. The patient then is free to do other things while the therapy is ongoing. No adverse effects have been reported. EMG-NMS is non- invasive and does not have any side effects.

###### Project B1

fMRI: Patients can experience claustrophobic feelings in an MRI-scanner. They get to wear protective earphones to exclude the beeping and knocking sounds of the apparatus. When patients have no metallic implants such as pacemakers (see exclusion criteria) the risks of MRI are minimal.

TMS: Some patients experience a slight tap on the head during TMS. The stimulation is painless. Although the risk of evoking epileptic insults in patients with a history or family history of epilepsy is precluded by the use of international safety standards, these patients are excluded from the study.

Project B2

Patients will get ample rest between measurements. The method is not invasive.

###### Project B3

Measurements with haptic robots take about 40 minutes including mounting and dismounting. The movement trajectory is a few centimetres. Patients can experience a little muscle-soreness for a few days after the measurement. The method is not invasive.

###### Project C

As there are no extra clinical measurements required, project C poses nu burdens or risks for participating patients

# 5. Statistical analysis

The database will be managed in Excel. The results of the haptic robot will be computed in MatLab first. The analysis will be conducted in SPSS.

Descriptive statistics will be performed on all subjects per project.

Further statistics include correlation and regression of clinical outcome variables (see paragraph 3)

*5.1 Project A: early intervention*

Power analysis:

Project A1: The number of patients is based on a statistical power of 80% (preventing Type II error) with an alpha of 5% (preventing Type I Error) for detecting a meaningful difference of 6 points (i.e., 10%) on the ARAT as the primary outcome measure. (Van der Lee et al, 1999) The population variance (a standard deviation of 8 points in the second week) is based on the findings of a randomized clinical trial in 102 stroke patients with a first-ever MCA stroke (measured with ARAT at 2 weeks post stroke). (Kwakkel et al, 1999; Kwakkel et al, 2003) Controlling for dependency between 5 repeated measurements in the first 5 weeks (test-retest reliability of 0.9 for ARAT based on 5 repeated measurements), a sample-size of 60 patients (including 10% drop outs) should be sufficient.

Project A2: On the basis of a previous cohort study with 101 first-ever MCA strokes (Kwakkel et al, 1999), patients with a poor prognosis have a probability of about 6% to regain some dexterity (ARAT > 9 points) at 6 months post stroke. We assume a proportional difference of 12% in favour of the experimental group. Based on a statistical power of 80% (preventing Type II Error) with an alpha of 5% (preventing Type I Error) and a test–retest reliability of 0.9 for ARAT with 5 repeated measurements, 120 patients should be enough to show statistical significance in favour of EMG-NMS in the poor prognosis group.

*5.2 Project B: cortical reorganisation and compensation strategies*

Power analysis

Project B1: The numbers needed for an fMRI study depend on the signal intensity of the volumes of interest (VOI).Our calculation is based on fMRI measures of Brodmann areas 9 and 46, which are primary association cortices. In these areas, the fMRI activation is assumed to be more difficult than in primary motor and sensory cortices. Therefore, our power analysis uses a conservative estimate of the number of subjects needed. The mean increment of the intensity of the signal in VOI (%) and the standard deviation of the normal signal intensity have both been found to be 1.5, whereas delta 'n' (i.e., the normalized minimal difference between groups that is detectable with fMRI) is estimated to be 1.15. Calculation of the required sample size is based on the formula {N=[2*(z(1-Alpha/2)-z(1-Beta))raise to square*(var(n)/delta)] in which Alpha (preventing type I error) and Beta (preventing type II error) are set at 0.01 and 0.10, respectively. This leads to a sample size of 13 patients in both the control and experimental groups. Based on an expected drop-out rate of 10%, we would need at least 30 stroke victims.

Project B3: Considering the parameter with the largest variability, i.e. reflex gains, a worst-case calculation of sample size, based on earlier measurements on stroke patients using haptic robots, reveals that the number of patients that needs to be measured is 10 in each ‘arm’ of the study, for an alpha of 5% (preventing Type I Error) and a beta of 10% (preventing Type II Error). This calculation is based on a standard deviation of 0.17 Nms/rad. (Meskers et al 2006) The smallest detectable difference will then be 0.12 Nms/rad (two-tailed). Controlling for 10% drop-outs groups of 30 from project A1 en 30 of project A2 should be sufficient.

*5.3 Project C: longitudinal relations*

To investigate the possible longitudinal association between recovery of dexterity on ARAT and covariates, bi-variate longitudinal regression analysis will initially be conducted, including ARAT change scores (i.e. first-order regression) and time-independent covariates at baseline, such as age, gender and lateralization of stroke, as well as change scores of the time-dependent covariates: MI-arm, FM-arm (including wrist), FM-hand, letter-cancellation task and Active Range of Motion (RoM) of trunk rotation and trunk bending during reaching. (Kollen et al, 2005; Kwakkel et al, 2006) Treatment intervention will be used as one of the covariates in the quasi-causal regression model. (Kwakkel, 1999.) Subsequently, standardized regression coefficients will be calculated and a multivariate, first-order regression model to predict functional change on ARAT will be developed. The -2log likelihood ratio test will be calculated to evaluate the necessity of allowing random regression coefficients into the model, and the Wald test will be used to obtain a P value for a particular regression coefficient. A two-tailed significance level of .05 will be used for all tests.

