#### Project A: early intervention

Project A1: (n=60) Patients with an upper limb deficit with an initially favourable prognosis (NIHSS arm score of 3 or 4 and/or ability to extend the wrist ≥ 10º) will be randomised into 2 groups:

- CIMT and conventional therapy.
- conventional therapy.

Project A2: (n=120) Patients with an initially poor prognosis for recovery of dexterity ((NIHSS arm score of 1 or 2 and/or inability to extend the wrist ≥ 10º) will also be randomized into 2 groups:

- EMG- NMS and conventional therapy;
- conventional therapy.

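### Project A2: 120 patients give about 53% power for 6% versus 18% return of dexterity, not the stated 80%

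*Protocol*

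**What the plan says.** The A2 paragraph of the power analysis in section 5.1 of the protocol gives these elements:

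- Control rate: "patients with a poor prognosis have a probability of about 6% to regain some dexterity", defined there as an ARAT score above 9 at 6 months.
- Effect: "We assume a proportional difference of 12% in favour of the experimental group".
- Error rates: 80% power, "with an alpha of 5% (preventing Type I Error) and a test–retest reliability of 0.9" with five repeated measurements.
- Result: "120 patients should be enough to show statistical significance in favour of EMG-NMS in the poor prognosis group".

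Section 4.5 confirms that 120 is the whole trial: "Project A2: (n=120) Patients with an initially poor prognosis for recovery of dexterity" are randomised into two groups. The research question for A2 in section 2.1 and the ARAT paragraph in section 3.1 fix the outcome as a binary status, 10 ARAT points or more, with the probability of return assessed at 6 months. The A2 paragraph does not say whether the test is one- or two-sided. Section 5.3 says "A two-tailed significance level of .05 will be used for all tests".

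**The concern.** With a 6% control rate and a 12-point difference, 60 patients per arm corresponds to about four expected responders in one group (60 × 0.06 = 3.6) and about eleven in the other (60 × 0.18 = 10.8). That is little information for 80% power at a 5% level, so the stated total looked too small.

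A2 is the larger of the two randomised trials, and this figure is the justification for its size on its primary outcome. If the true power is near one half, the trial would miss a tripling of the return of dexterity about as often as it would find it. A reader who relies on the stated 80% would give a non-significant result more weight than it deserves.

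**Working it through.** **Inputs.** p1 = 0.06, difference 0.12 and so p2 = 0.18, alpha 0.05, power 0.80, total 120 (all from section 5.1). Two-sided testing comes from section 5.3. Equal allocation, 60 per arm, is assumed because section 4.5 names two groups but no ratio. Reading 12% as percentage points is also an assumption; the other readings are tested below and are worse.

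**Attempt to reproduce 120.** With mean rate 0.12, the pooled-variance formula is

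n per arm = [1.96 × √(2 × 0.12 × 0.88) + 0.842 × √(0.06 × 0.94 + 0.18 × 0.82)]² / 0.12²

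= [1.96 × 0.4596 + 0.842 × 0.4517]² / 0.0144 = 113.9,

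so 114 per arm and 228 in total. Other standard versions do not give 120 either:

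| Formula, 80% power | Two-sided total | One-sided total |
|---|---|---|
| Pooled normal | 228 | 180 |
| Unpooled normal | 224 | 176 |
| Arcsine | 216 | 172 |
| Pooled with continuity correction | 262 | 212 |

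**Power at the planned size.** z = (0.12 × √60 − 1.96 × 0.4596) / 0.4517 = (0.9295 − 0.9007) / 0.4517 = 0.064, so power = Φ(0.064) = 52.5%.

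| Patients per arm | Normal, two-sided | Chi-square, exact power | Fisher's exact | Normal, one-sided |
|---|---|---|---|---|
| 60 | 53% | 54% | 42% | 65% |
| 54 (10% lost) | 48% | 49% | 36% | 61% |

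With 120 per arm, the normal approximation gives 82%. A per-arm figure entered as the total would therefore explain the number, but that is conjecture and nothing below depends on it.

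**Detectable difference.** At 60 per arm, two-sided power is 79.6% for 6% versus 24%. It reaches 80% at an experimental rate of 24.1%, a difference of about 18 points.

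**Repeated measurements.** The mean of five measurements correlated at 0.9 has variance factor (1 + 4 × 0.9)/5 = 0.92. This gives 113.9 × 0.92 = 104.8, so 105 per arm. Power at 60 per arm becomes 56% two-sided, or 68% one-sided. To bring 228 down to 120 the factor would have to be 120/228 = 0.53. In the same formula that means a correlation of (5 × 0.53 − 1)/4 = 0.41, not 0.9.

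**Other readings of the 12%.** If 12% is the experimental rate (6% versus 12%), power at 60 per arm is 21% and 80% power needs 712 patients. If it is a relative increase (6% to 6.7%), power is negligible.

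**Drop-out.** A1, B1 and B3 each allow for 10% loss and A2 does not. With 10% loss, 228 becomes 228/0.9 = 253.3, or 254 to keep the arms equal.

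**The case against.** The best defence is that the A2 paragraph leaves sidedness open and speaks of significance in favour of EMG-NMS, which could be read as directional. The two-tailed rule stands under Project C. This is fair, and the one-sided figure belongs beside the two-sided one. It does not rescue the claim: one-sided power is 65%, or 68% with the 0.92 factor added.

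A second defence is that no formula is given for the repeated-measurements credit, so another version might give fewer patients. That is true. A factor of 1 − 0.9² = 0.19, as in an adjustment for a baseline covariate, gives about 43 patients in total (228 × 0.19). But that does not reproduce 120 either, and it applies to a continuous outcome, not to whether one patient is above a threshold at one visit. What stands is that one cannot say every conceivable credit fails; one can say that the credit is unspecified, does not fit this endpoint, and in its usual averaging form is worth only 8% of the variance.

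It is also fair that the origin of 120 is unknown, that how readers would take a null result is a prediction, and that reporting detail may sit in a statistical analysis plan not seen here. None of this bears on the mismatch between the stated inputs and the stated number.

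**Conclusion.** The sample-size statement for A2 is wrong as written. On the protocol's own inputs, 120 patients give about 53% power two-sided (42% to 55% across the two-sided tests tried) and 65% one-sided. The stated 80% needs 228 patients before any loss, so the plan has roughly half the number that its assumptions require.

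The conclusion rests on equal allocation and on reading the 12% as an absolute difference. The other readings of the 12% lower the power. None of the standard two-proportion formulas, with either sidedness and with or without the averaging credit, gives 80% power at 120.

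**What to change.** In section 5.1, Project A2:

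1. State that 120 patients (60 per arm) give about 53% power for 6% versus 18% at two-sided 5%, about 48% after 10% loss, and 80% only for about 6% versus 24%. Write the 12% explicitly as percentage points, and name the sidedness and allocation ratio.
2. Delete the reference to test-retest reliability and five repeated measurements for this binary endpoint.
3. Say that the result will be reported as a difference in proportions with a 95% confidence interval, and that a non-significant result does not exclude a 12-point benefit. For illustration, observed rates of 6% and 12% with 60 per arm give a difference of 6 points ± 1.96 × √[(0.06 × 0.94 + 0.12 × 0.88)/60] = 6 ± 10 points. That interval contains both 0 and 12.

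The cost is a reworded paragraph and a less favourable power statement; no extra patients are needed. The rewording corrects the figure but does not add power. If the sponsor wishes to keep 80% power for a 12-point difference, the total has to rise to 228, or 254 with 10% loss, and the n in section 4.5 has to change with it.

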No studies have so far analysed in detail whether improvement in dexterity reflects reduction of basic motor impairments or works by learning compensatory movement strategies. To date, there is a growing weight of evidence in favour of compensatory learning strategies (Kwakkel et al, 2004; Sunderland, 2005). For example, there are strong indications that motor recovery after cortical injury occurs to a large extent through behavioural compensation strategies, rather than via processes of true recovery alone (Kwakkel et al, 2004b; Sunderland, 2005; Geurts et al, 2005). Theoretically, behavioural compensation strategies in which deficits are taken over by motor control of the less-affected trunk are considered to be potential confounders in our understanding of ‘neural repair’ and related cerebral recovery after stroke (Kwakkel et al, 2004; Sunderland, 2005). For example, in one recent study of stroke patients, moderately to severely impaired subjects used compensatory strategies of the trunk to accomplish a pointing task, rather than trying to achieve restitution of the original arm function (Cirstea et al, 2000, 2003). Cortical changes detected by fMRI may therefore reflect alternative (compensatory) motor skill learning rather than restitution of stroke induced impairments. As a result, these studies fail to differentiate between ‘motor recovery based on true repair’ and ‘motor recovery based on using compensation strategies’. This has caused considerable difficulty in the interpretation of such changes in fMRI studies, apart from other potential confounding factors such as a lack of control over mirror movements, strength, precision and the timing of imaginary movements (motor paradigm) during fMRI scanning. Finally, understanding the observed adaptive behavioural movement strategies requires that the biomechanical changes of the musculoskeletal system are measured longitudinally. For this purpose, it is of vital importance to understand the relationship between parameters characterizing CNS function (such as TMS and fMRI) and parameters describing end-point mechanical behaviour and peripheral reflex-chain properties.

Project B1: fMRI/TMS

*Research questions:*

1. Are CIMT-induced gains reinforced by recruitment of cortical activation in the ipsi-lesional hemisphere compared to patients receiving usual care?

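### The inputs stated for Project B1's fMRI sample size give 23 to 25 patients per group, not 13; 13 per group has about 56% to 64% power, not 90%

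*Protocol*

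**What the plan says.** Protocol section 5.2, under Project B1, gives the inputs, a formula and a result.

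- Error rates: "Alpha (preventing type I error) and Beta (preventing type II error) are set at 0.01 and 0.10, respectively". The formula uses z(1-Alpha/2), so the test is two-sided.
- Effect size: "the normalized minimal difference between groups that is detectable with fMRI) is estimated to be 1.15".
- Variability: the mean signal increment and "the standard deviation of the normal signal intensity have both been found to be 1.5".
- Formula: "N=[2*(z(1-Alpha/2)-z(1-Beta))raise to square*(var(n)/delta", with the bracket then closed.
- Result: "This leads to a sample size of 13 patients in both the control and experimental groups".
- Total: "Based on an expected drop-out rate of 10%, we would need at least 30 stroke victims".

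The between-group question this serves is the first B1 research question in section 2: "Are CIMT-induced gains reinforced by recruitment of cortical activation in the ipsi-lesional hemisphere compared to patients receiving usual care". Section 4.5 invites 30 patients each from A1 and A2 into Project B, and says that "only patients that can extend their wrist beyond 10 degrees and fingers beyond 20 degrees will be asked to participate in the fMRI measurements".

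**The concern.** A sample-size formula for comparing two means adds the two normal quantiles and divides by the square of the difference. The printed one does neither, and its literal value is nowhere near 13. The inputs can also be put into the correct formula, and the answer is still far from 13.

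fMRI is listed among the primary outcome measures of Project B in section 3.2, and the CIMT comparison is a randomised treatment question. A reader who takes 90% power at alpha 0.01 at face value would read a null result as fairly strong evidence that CIMT does not recruit ipsilesional cortex. With the planned numbers the design does not support that reading for a difference of the stated size.

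**Working it through.** **Inputs, all from section 5.2, Project B1.** Alpha = 0.01 two-sided, so z(0.995) = 2.576. Beta = 0.10, so z(0.90) = 1.282. Delta = 1.15, described as normalized. Variance on the normalized scale is taken as 1, because the SD and the mean increment are both 1.5.

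**Step 1: the printed formula, taken literally.**
2 × (2.576 − 1.282)² × 1 / 1.15 = 2 × 1.675 / 1.15 = 2.9. This is about 3, not 13. Using the raw variance 1.5² = 2.25 instead gives 6.6, which is not 13 either.

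**Step 2: attempts to reproduce 13.** The protocol does not show the step. Two routes fit equally well:

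- Plus sign, delta still unsquared: 2 × (3.857)² / 1.15 = 2 × 14.879 / 1.15 = 25.88. Half of this is 12.94.
- Correct formula with z = 1.645 in place of 2.576 (one-sided alpha 0.05): 2 × (1.645 + 1.282)² / 1.15² = 12.95.

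The first halves a number that the factor 2 already makes a per-group number. The second uses an alpha other than the stated one. Neither matches the text.

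**Step 3: the correct formula with the stated inputs.**
N per group = 2 × (z(1−alpha/2) + z(1−beta))² × var / delta² = 2 × 14.879 / 1.3225 = 22.5, so 23 per group. With the exact two-sample t-test, 24 per group gives 89.7% and 25 gives 91.1%, so 25 are needed.

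**Step 4: totals.** 2 × 23 = 46 and 2 × 25 = 50 completers. With 10% drop-out, 46/0.9 = 51.1 and 50/0.9 = 55.6, so 52 to 56 patients. The protocol's own step, 26/0.9 = 28.9 and then 30, is consistent with its 13; the error lies before it.

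**Step 5: what the planned numbers deliver for a normalized difference of 1.15.**

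| Per group | Two-sided alpha | Power, exact t | Power, normal |
|---|---|---|---|
| 13 | 0.01 | 56% | 64% |
| 15 (all 30 evaluable) | 0.01 | 65% | 72% |
| 13 | 0.05 | 80% | 83% |
| 15 | 0.05 | 86% | 88% |

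The normalized difference detectable at the stated alpha and beta is 1.63 with 13 per group and 1.50 with 15 (exact t), or 1.51 and 1.41 by the normal approximation.

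**Step 6: which patients count.** In section 4.5, CIMT is randomised only in A1. Thirty A1 patients are invited into Project B, which is about 15 per arm before drop-out and before the wrist and finger criteria for scanning. The 30 A2 invitees are randomised to a different treatment and add nothing to the CIMT comparison.

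**The case against.** Several points on the other side have force.

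- **The cause of 13.** A reader might infer that the sponsor halved a per-group number. The document does not support that as a fact: no halving is shown, and an alpha that was misreported in the text would explain 13 just as well with sound arithmetic. What stands is only that the stated inputs and the stated result disagree.
- **The minus sign.** It may be a notation slip, since neither reconstruction of 13 uses it. It is still wrong as printed and should be corrected.
- **Exact t or normal.** The protocol's formula is a normal approximation, under which the power of 13 per group is 64%, not 56%. The method must be named, but neither figure is near 90%.
- **Units of delta.** One could read 1.15 as raw signal units against an SD of 1.5, which would make the shortfall far larger. The text calls the difference normalized, so that reading is not supported.
- **The word conservative.** A reader might take it as a false claim about the calculation. It refers to basing the inputs on brain areas where activation is assumed harder to detect. That is a legitimate argument about the inputs, but no motor-cortex figure is given that would offset the shortfall.
- **Scanning capacity.** It is tempting to say that no A2 patient can be scanned. Section 4.5 joins the A2 criteria with and/or, so A2 may include patients who can extend the wrist. No cap on B1 scanning overall follows; the limit applies to the CIMT question.
- **Importance.** Only the first of the five B1 questions compares treatment groups, and the summary describes the mechanistic work as exploratory. Section 5.3 sets a two-tailed 0.05 level for all tests, though it is unclear whether that reaches B1. At 0.05 the power is 80% to 86% (exact t), which is respectable, but it is not what section 5.2 claims.

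**Conclusion.** The point holds. With two-sided alpha 0.01, beta 0.10 and a normalized difference of 1.15, a two-group comparison needs 23 patients per group (normal) or 25 (exact t). The stated 13 gives 56% or 64% power, and 15 per group gives 65% or 72%, against 90% claimed. By exact t at 13 per group, a true difference of the planned size would be missed about 44% of the time rather than 10%.

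This assumes equal groups, a normalized variance of 1 and a simple comparison of two means, as the protocol's own formula implies. How 13 was reached cannot be determined from the document, and the conclusion does not depend on it.

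**What to change.** In section 5.2, Project B1:

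1. Print the formula as N per group = 2 × (z(1−alpha/2) + z(1−beta))² × var / delta², with var = 1 on the normalized scale.
2. Replace the claim for 13 per group with what 30 patients deliver, and name the method. One of these would do:
   - about 56% to 65% power (exact t, 13 to 15 per group) at two-sided alpha 0.01 for a normalized difference of 1.15;
   - about 80% at two-sided alpha 0.05 with 13 per group, 86% with 15 (exact t);
   - a detectable normalized difference of about 1.5 to 1.6 at the stated alpha and beta (exact t).
3. If 13 came from a different alpha, state that alpha.
4. Say that conservative refers only to the choice of brain region and does not offset the shortfall.
5. State that the CIMT comparison rests on the A1 patients in Project B.

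This changes wording only, with no change in enrolment or scans. The cost is a less favourable stated power.

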2. Is it possible to explain the recovery of dexterity in the paretic extremity during the first 6 months post stroke from the changes in cortical activation found in the first 4 weeks on fMRI in M1, vPMA, dPMA and SMA cortices of infarcted and non-infarcted cerebral hemispheres in patients with primary ischemic middle cerebral artery stroke?
3. Are changes in fMRI patterns in the contra-lesional cortex (M1) related to the impact of cortico-spinal tract degeneration as established with TMS within the first week and at 6 months post stroke?
4. What is the predictive value of TMS parameters such as motor threshold, motor evoked potential (MEP) and the subsequent ‘silent period’ (cortical inhibition phenomenon) for functional outcome at 6 months?
5. Which muscles of the paretic limb (i.e., intrinsic hand muscles, finger and wrist extensors or upper arm muscles) are most sensitive and specific in predicting functional outcome at 6 months post stroke?

Project B2: kinematics

*Research questions:*

1. Can functional improvement of the paretic arm during the first 6 months be explained by behavioural strategies to compensate for deficits (e.g., bending and rotating the trunk) in a standardized reaching task?
2. What is the relation between kinematic changes observed during functional recovery and dynamic changes in cerebral motor networks?

Project B3: haptic robot

*Research questions*

1. How and to what extent do endpoint mechanical behaviour (at the wrist joint) and peripheral reflex chain properties change during follow-up after stroke?
2. Does CIMT or EMG-NMS affect endpoint mechanics and peripheral reflex chain properties?
3. How do endpoint mechanics relate to upper limb performance in executing a reaching task?
4. How are these parameters and changes in parameters in the course of time influenced by CMIT or EMG-NMS?

*2.3 Project C: longitudinal relations. Objective: analysing the longitudinal relations between the results of project B.*

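### Project B3: 10 patients per arm gives about 32% power, not 90%, for a difference of 0.12 Nms/rad, and the difference detectable with 90% power is about twice that

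*Protocol*

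**What the plan says.** The Project B3 paragraph of Protocol section 5.2 takes reflex gain as the most variable parameter and presents a worst-case sample-size calculation. It concludes that "the number of patients that needs to be measured is 10 in each ‘arm’ of the study". The error rates it sets are 5% for type I and 10% for type II. It adds that "This calculation is based on a standard deviation of 0.17 Nms/rad" and that "The smallest detectable difference will then be 0.12 Nms/rad (two-tailed"). On enrolment it says: "Controlling for 10% drop-outs groups of 30 from project A1 en 30 of project A2 should be sufficient".

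Two other places show which comparison is meant. Section 2.2, under Project B3, asks: "Does CIMT or EMG-NMS affect endpoint mechanics and peripheral reflex chain properties"? Section 4.5 says of Project A1 that its patients "will be randomised into 2 groups" and gives Project A2 the same two-group structure. It takes 30 patients from each trial into Project B.

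**The concern.** A difference of 0.12 against a standard deviation of 0.17 is a standardised difference of 0.71. Ten patients per arm is far too few to detect that with 90% power in a two-group comparison.

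Reflex gain is the haptic outcome named as primary for Project B in section 3.2, and two of the four B3 research questions ask about the effect of treatment. Patients are to be measured at eight visits (section 4.6), about 40 minutes each, with possible muscle soreness afterwards (section 4.7). If the power claim is wrong, a non-significant result would be read as ruling out an effect of 0.12 when the study had little chance of finding one.

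**Working it through.** **Inputs**, all from Protocol section 5.2 (Project B3) unless noted:

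- n = 10 per arm
- two-sided alpha 5%, so z = 1.960
- beta 10%, so z = 1.282
- SD = 0.17 Nms/rad and difference = 0.12 Nms/rad
- drop-out 10%
- 30 patients per trial in two groups (section 4.5). No allocation ratio is given, so an equal split of 15 per arm is assumed, or about 13 per arm after drop-out (30 × 0.9 = 27).

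**1. Sample size for the stated difference and power.** n per arm = 2 × (1.960 + 1.282)² / (0.12/0.17)² = 42.2, rounded up to 43. The t-test needs 44. With 10% drop-out this becomes 48 or 49 per arm. The stated 10 is not reproduced.

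**2. Power at 10 per arm.** The standard error is 0.17 × √(2/10) = 0.0760, and 0.12/0.0760 = 1.58. By normal approximation, power = Φ(1.58 − 1.96) = 35%. With the noncentral t distribution it is 32%.

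**3. Difference detectable with 90% power at 10 per arm.** 0.17 × √(2/10) × (1.960 + 1.282) = 0.246, or 0.261 by t-test. That is 2.05 to 2.17 times the printed 0.12.

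**4. The numbers to be enrolled.**

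| Patients per arm | Power for 0.12 (t-test) | Power for 0.12 (normal) | Difference detectable with 90% power (normal / t) |
|---|---|---|---|
| 10 | 32% | 35% | 0.246 / 0.261 |
| 13 | 41% | 44% | 0.216 / 0.225 |
| 15 | 46% | 49% | 0.201 / 0.208 |

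**5. Other readings of the calculation**, each with SD 0.17 and difference 0.12:

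- One-sided test at 90% power: 35 per arm.
- Two-sided test at 80% power: 32 per arm.
- One-sided test at 80% power: 25 per arm.
- One-sample or paired test with 0.17 as the relevant SD: 22 patients by normal approximation, 24 by t-test. Power at n = 10 is 51%.
- The formula printed for Project B1 in the same section, with its minus sign, its variance/delta term, or both: 1.8, 5.1 or 0.2.
- Comparison of 30 with 30 patients: 77% power, or 72% with 27 per group after drop-out.
- Baseline-adjusted analysis, which multiplies the variance by 1 − r²: 10 per arm is enough only if r is about 0.875, since 42.2 × (1 − 0.875²) = 9.9. At r = 0.5 it takes 32 per arm, at r = 0.7 it takes 22, and at r = 0.8 it takes 16.

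**6. Where the printed figures may come from.** Two routes come close, and neither is the calculation described.

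- The half-width of a 95% interval for the mean of one group of 10 is 2.262 × 0.17/√10 = 0.1216. It contains neither a second arm nor a power term.
- With the two values interchanged (difference 0.17, SD 0.12), n = 2 × (1.960 + 1.282)² / (0.17/0.12)² = 10.5, so 11 per arm.

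The Protocol shows no formula for B3, so either source is an inference.

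**The case against.** The strongest reply is that the paragraph names no test. Each patient is measured eight times, and some B3 questions concern change over time, so a repeated-measures analysis could be more efficient than a comparison at one time point. That is true in principle. But 10 per arm would need a within-patient correlation near 0.875 under baseline adjustment, and the B3 paragraph gives none. The Project A1 and A2 paragraphs do state a test–retest reliability, so an unstated adjustment cannot be presumed here.

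A second reply is that actual enrolment exceeds 10 per arm, and that the research question could be read as treated patients pooled across both trials against pooled controls, about 30 with 30. The Protocol does not state such pooling, and on that reading power is still only 72–77%.

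Third, the source of the error is unknown. If the standard deviation and the difference were transposed, the inputs need correcting and the sample size does not. This stands, and the fix allows for it.

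Fourth, B3 is a mechanistic sub-study. This also stands: the ARAT comparisons in A1 and A2 have their own sample sizes and are unaffected.

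**Conclusion.** The concern holds. On the Protocol's own inputs, 10 per arm gives about 32% power for 0.12 Nms/rad where 90% is claimed, and the difference detectable with 90% power is about 0.25–0.26. Reaching 90% power for 0.12 would take 43–44 evaluable patients per arm. The planned enrolment leaves power between 41% and 46%, so the study would miss the stated difference more often than it found it.

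These figures assume a two-group comparison of means at one time point with SD 0.17 in each arm. The 41–46% also assumes an equal split of the 30 patients in each trial. No reading that uses only the stated inputs reproduces 10 per arm.

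**What to change.** First check 0.17 and 0.12 against the measurements they were taken from, and correct them if they were interchanged. In that case 11 per arm by normal approximation would be enough, and the planned enrolment covers it.

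If the inputs stand, rewrite the paragraph to:

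- name the comparison (treated against control within each trial) and the follow-up visit it refers to;
- state that, with SD 0.17 and two-sided alpha 5%, the smallest difference detectable with 90% power is about 0.20–0.21 Nms/rad at 15 per arm and 0.22–0.23 at 13 per arm after drop-out;
- state that power for 0.12 is about 41–46%, and drop the claim that the numbers suffice for 0.12 at 90% power.

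Precision can be improved without new data by adjusting follow-up reflex gain for the week-1 haptic measurement already scheduled. Therapy is also listed from week 1 in section 4.6, so the plan should confirm that this measurement precedes treatment. A gain from the adjustment should be quoted only with a stated and sourced within-patient correlation.

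The cost is the wording of one paragraph and, if adopted, one covariate in the analysis. No extra patients or visits are needed.
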